#### Confidentiality {27}

Each participant will be given a code upon enrolment. The statistics team will only see patient codes, and real information will not be disclosed.

### Plans for collection, laboratory evaluation, and storage of biological specimens for genetic or molecular analysis in this trial/future use {33}

As described above “Additional consent provisions for collection and use of participant data and biological specimens {26b}” section, there will be no biological specimens collected.

### Statistical methods

#### Statistical methods for primary and secondary outcomes {20a}

The primary outcome of this study is the occlusion rate in 7 days. The calculation formula is:$$\mathrm{Occlusion}\;\mathrm{rate}=\frac{\mathrm{Complete}\;\mathrm{occlusion}+\mathrm{Partial}\;\mathrm{occlusion}}{\mathrm{Number}\;\mathrm{of}\;\mathrm{enrolled}\;\mathrm{cases}}\times100\%$$

A superiority test will be conducted on the occlusion rate of the two groups. The chi-square test will be used to compare the occlusion rates between the two groups. The occlusion rate and 95% confidence interval will be calculated for the intervention group. Simultaneously, the 95% confidence intervals (CIs) for the difference in the occlusion rate between the test group and the control group will be calculated. If the upper limit of the confidence interval is less than the superiority threshold (0), the conclusion of superiority is deemed valid.

Validity analysis will be conducted on both the full analysis set (FAS) and per protocol set (PPS). All baseline demographic data analysis will be conducted on the FAS, and safety evaluations will be based on the safety analysis set. The FAS refers to the set of subjects analysed according to the intention-to-treat (ITT) principle, including all subjects who will be randomized and intervened. For subjects who failed to complete the full efficacy evaluation, non-responder imputation (NRI) will be used to handle the missing data.

With respect to the secondary outcomes, comparisons between the two groups will be made using the group *t* test or Wilcoxon rank-sum test for measurement data according to distribution and the chi-square test or Fisher’s exact probability method for count data. 

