## Introduction

### Background and rationale {6a}

Maintaining unobstructed venous access is of great clinical importance [1, 2]. The central venous catheter is widely used in clinical practice, with single-lumen, double-lumen, and multi-lumen, and can be used for monitoring hemodynamic, infusion therapy, blood transfusion, chemotherapy, and parenteral nutrition [3, 4]. The complications associated with central venous catheters can reach 40% [5], and common complications include occlusion, infection, and catheter dislodgement [6], with occlusion occurring in 25% to 38% of cases [7]. Blockage of a catheter can affect the patient’s treatment [8] or, worse, can threaten the patient’s life and increase health care costs [9].

The central venous catheter occlusion factors can be divided into intrinsic and extrinsic factors. Intrinsic factors, such as advanced age, female sex, hypercoagulable blood, and disease, are related to the patients themselves and can lead to an increased probability of catheter occlusion [10]. Extrinsic factors include the catheter placement site, number of punctures, catheter folding, improper flushing, and nature of the infused drug [11, 12]. Improper flushing, for example, failure to flush the lumen in a timely manner, failure to use the correct locking solution, or failure to use the correct flushing technique, can increase the probability of catheter occlusion [13, 14]. In addition, infusion of specific drugs can also lead to occlusion; for example, infusion of drugs that are hypertonic, too high, or too low in pH can easily lead to changes in plasma osmolality, thrombus formation, catheter tip occlusion, or haemagglutination occlusion [15].

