#### Sample size {14}

The primary outcome is the rate of catheter occlusion within 7 days. A preliminary study with a small number of patients (20 patients) indicated that the catheter occlusion rate was 0 in the test group and 20% in the control group. According to an expert consensus [7], the occlusion rate in the control group ranged from 25 to 38%. Using an estimation procedure based on the differences between the two groups, the necessary sample size was determined. An occlusion rate of 10% was assumed in the test group, and an occlusion rate of 25% was assumed in the control group. A minimum sample size of 125 participants per group (250 participants total) was calculated by PASS 15 software (NCSS, LLC) to provide sufficient statistical power for detecting the difference between the two groups. This was done by setting the single-sided significance level (*α*) at 0.025 and the statistical power (1-*β*) at 0.8 while taking into consideration a dropout rate of 20%.

The sample size was calculated as follows:$${n}_{T} = {n}_{C}=\frac{{({Z}_{1-a/2}+ {Z}_{1-\beta })}^{2} \left[{P}_{C}\left(1-{P}_{C}\right)+{P}_{T}(1-{P}_{T}) \right]}{{\left(\left|D\right|-\Delta \right)}^{2}}$$

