### Assignment of interventions: allocation

#### Sequence generation {16a}

Before the start of the study, the statistics team will perform randomization using a computer-generated random assignment list at a 1:1 ratio.

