#### Concealment mechanism {16b}

The statistics team will generate random numbers and will hand them over to people unrelated to the study, who will then make sealed, opaque envelopes, and send them to each centre in order of the centres’ initials. Each centre will receive 18 envelopes. The random envelopes will be kept by the principal investigators (PIs) of each centre and will not be accessible to persons unrelated to this study. The statistics team will not be involved in clinical trials.

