## Discussion

Although PICCs and totally implantable venous access devices (TIVADs) are both better than CVCs in terms of the occlusion rate [26, 27], PICCs and TIVADs are more suitable for long-term infusion therapy patients, while CVCs are more suitable for short-term infusion therapy and surgery patients. A 25–38% occlusion rate was found for the CVC, and a new flushing and locking technique was designed to solve this problem. The conventional catheter flushing technique involves flushing the catheter before and after infusion or under other special circumstances. Considering that the pulsatile flushing technique requires a certain amount of operator skill and that occlusion may occur during drug infusion, we wonder if it is possible to design a technique for continuous flushing so that the catheter is always flushed and whether the drug is being infused, which effectively prevents catheter occlusion. Conventional KVO infusion may result in haemodilution or fluid overload; therefore, we will use an elastic pump with a volume of 50 ml, a flow rate of 2 ml/h, and maintain the infusion pressure at 55 kPa, which is greater than the central venous pressure to replace conventional KVO infusion.

This study offers a completely new way to flush and lock catheters. In this way, the nurse only has to learn to attach and remove the elastic pump, saving time by not having to flush the catheter as often. From a theoretical point of view, continuous flushing might be a good way to avoid catheter occlusion. We hope this study will provide an evidence-based basis for catheter maintenance.

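### The unadjusted primary comparison is valid, but it leaves a little precision unused by ignoring the baseline predictors of occlusion that the protocol itself names and collects

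*Protocol article*

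**What the plan says.** Statistical methods for primary and secondary outcomes {20a} fixes the primary test: "The chi-square test will be used to compare the occlusion rates between the two groups". The decision rests on the interval for the difference in rates: "If the upper limit of the confidence interval is less than the superiority threshold (0), the conclusion of superiority is deemed valid". Neither that section nor those on data management {19}, additional analyses {20b} and missing data {20c} mention a centre term, a stratified test or a baseline covariate.

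Allocation comes from a "computer-generated random assignment list at a 1:1 ratio" (Sequence generation {16a}), and under Concealment mechanism {16b}, "Each centre will receive 18 envelopes". Blocking or stratification by centre is neither stated nor ruled out.

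On predictors of the outcome, Background and rationale {6a} says: "Intrinsic factors, such as advanced age, female sex, hypercoagulable blood, and disease, are related to the patients themselves", and that these can raise the chance of occlusion. Study setting {9} mixes intensive care, surgical and oncology wards. The participant timeline (Table 2) records demographics and a coagulation panel that includes D-dimer before the study period. The Discussion adds that "the pulsatile flushing technique requires a certain amount of operator skill".

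**The concern.** The protocol identifies patient characteristics that it expects to influence occlusion and measures several of them before treatment. It then fixes a primary analysis that uses none of them. When a baseline variable predicts the outcome, adjusting for it narrows the interval for the treatment difference without changing the question asked. The plan was sized for 80% power after dropout, with no further reserve, so a small gain from data already in hand is worth having.

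The handling of centre raises a related question. There are 14 centres with 18 envelopes each, and the text does not say whether arms were balanced within centre. If they were, a test that ignores centre uses a standard error that is somewhat too large. What is at stake is precision and, in that case, some unused type I error. The validity of the primary test is not at stake.

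**Working it through.** **1. The plan's own figure.** Inputs from Sample size {14}: "An occlusion rate of 10% was assumed in the test group, and an occlusion rate of 25% was assumed in the control group". Alpha is 0.025 one-sided (equal to 0.05 two-sided), power 0.80, dropout 20%.

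- Pooled-variance formula: n = [1.960 × √(2 × 0.175 × 0.825) + 0.842 × √(0.25 × 0.75 + 0.10 × 0.90)]² / 0.15² = (1.053 + 0.443)² / 0.0225 = 99.5, so 100 per group.
- Dropout: 100 / 0.80 = **125 per group**, an exact match.
- The printed unpooled formula gives 97, then 122 after dropout, within 3% of 125.
- Power is 80.2% with 100 per group and 88.2% with 125.

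The sample size therefore assumes the same unadjusted comparison as the analysis section. Design and test agree.

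**2. Chance imbalance by centre, if the list was unblocked.** With X ~ Binomial(18, 0.5), P(X ≤ 6 or X ≥ 12) = 0.238. Across 14 centres, 14 × 0.238 = 3.3 would be expected to split 12:6 or worse.

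**3. Does this harm the test?** A simulation of 14 centres × 18 = 252 patients, 20,000 runs per setting, compared three analyses: the chi-square test, a Cochran-Mantel-Haenszel (CMH) test by centre, and a linear model with centre and one covariate (robust standard errors). The documents give no centre or covariate effects, so these were assumed: centre SD 0, 0.5 or 1.0 on the logit scale, and covariate log-odds 0 or 0.7 per SD.

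Type I error of the chi-square test (nominal 5%, both arms at 25%):

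- simple or single-list allocation: 4.8 to 5.2% in every setting;
- balanced within centre: 5.1 to 5.2% (SD 0), 4.4 to 4.6% (SD 0.5), 3.5 to 3.7% (SD 1.0).

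It is never materially above nominal, and it is conservative if arms were balanced within centres that differ.

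**4. What adjustment buys.** Power (%) at 25% versus 10%, all 252 analysed, selected settings:

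| Centre SD | Covariate log-odds | Allocation | Chi-square | CMH by centre | Centre + covariate |
|---|---|---|---|---|---|
| 0 | 0 | single list | 89.3 | 87.7 | 87.8 |
| 0 | 0 | balanced in centre | 89.4 | 89.6 | 89.6 |
| 0 | 0.7 | single list | 89.2 | 87.9 | 89.9 |
| 0 | 0.7 | balanced in centre | 89.3 | 89.5 | 91.4 |
| 1.0 | 0 | single list | 88.6 | 90.6 | 90.6 |
| 1.0 | 0 | balanced in centre | 89.9 | 92.1 | 92.1 |
| 1.0 | 0.7 | single list | 88.5 | 90.2 | 91.6 |
| 1.0 | 0.7 | balanced in centre | 89.6 | 91.4 | 93.0 |

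Over all 18 settings:

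- CMH minus chi-square runs from -1.8 points (89.32 to 87.51; simple allocation, no centre effect) to +2.2 points (89.92 to 92.13; balanced, SD 1.0).
- The last column minus the CMH column isolates the covariate. It is 1.4 to 2.0 points when the covariate matters and between 0.0 and 0.2 when it does not.
- Centre and covariate together, against chi-square, run from -1.7 to +3.4 points.

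**5. Why centre alone can cost power.** On an unblocked list the expected Mantel-Haenszel information per centre is (18 - 1)/4 = 4.25, so 14 × 4.25 = 59.5. The unstratified comparison has (252 - 1)/4 = 62.75. The loss is 1 - 59.5/62.75 = 5%, and real centre differences must outweigh it.

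**6. Size in patients.** Power rises from 88.18% at 125 per group to 88.43% at 126, about 0.25 points per additional patient per arm. A gain of 1 to 2 points is then worth about 4 to 8 patients per arm.

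**7. Room for a model.** At the design rates, 125 × 0.25 + 125 × 0.10 = 44 occlusions are expected. Age, sex, ward type (two terms) and D-dimer add five terms to treatment, so about 44/6 = 7 events per term. That supports a short fixed list and argues against adding 13 centre indicators to it.

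**The case against.** The strongest reply is that nothing here is wrong. An unadjusted chi-square test is sound after 1:1 randomisation, the sample size assumes it, and chance imbalance is already reflected in the standard error. This stands, and it limits the point to efficiency. It is also fair that supporting adjusted analyses may sit in an analysis plan that is not shown. But the primary analysis itself is fixed in the article, so its choice can be discussed.

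Several stronger readings are tempting, and the documents do not support them:

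- *Centre imbalance biases the result.* Step 3 shows the level held at about 5% even with strong centre effects.
- *Eighteen envelopes per centre means centre is a stratum the analysis must follow.* The text describes one list cut into sets. Stratification is not stated, so no mismatch between randomisation and analysis is shown. Equally, the 24% imbalance figure holds only if the list was unblocked.
- *Operator skill makes a centre term essential.* The Discussion ties skill to the control technique, which points to a treatment effect that may differ by centre. A common centre-stratified difference does not address that. The adherence section {11c} also sets out training, videos and coordinator checks.
- *Adjustment would lift power from about 81% to 83-85% at no cost.* That requires centre and baseline factors to explain 5 to 10% of outcome variance, which the documents do not give. It omits the loss in step 5, and stratifying by centre alone would not deliver it.

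**Conclusion.** The primary test and rate difference are valid, and neither type I error nor the sample size is called into question. Within that limit, the plan leaves a modest amount of precision unused. Adjusting for a prognostic baseline covariate is worth about 1 to 2 points of power, with essentially no loss if the covariate proves uninformative. CMH by centre is worth about -2 to +2 points, so making it the primary analysis regardless of how the list was built is not justified.

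These figures rest on assumed effects (centre SD up to 1.0 on the logit scale, one covariate at 0.7 log-odds per SD) and on 252 patients analysed at the design rates. They do not describe the full analysis set once missing outcomes are counted as occlusions under section {20c}. The simulation used a linear model with centre, not the logistic model proposed below. Both give a risk difference, and the covariate gain is expected to be similar.

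**What to change.** - Prespecify as the primary estimate a standardised risk difference with 95% interval from a logistic model with treatment, age, sex, ward type and baseline D-dimer. Keep the existing rule that the upper limit must lie below 0. Fix the covariate list and its coding in advance, and keep the plain chi-square test as supportive.
- Trial status gives data collection as complete on July 31, 2023. If analysis has already begun, leave the chi-square analysis primary and add the adjusted risk difference as a named sensitivity analysis.
- State whether the list was blocked or stratified by centre. If it was, account for centre in the primary analysis (CMH with a Mantel-Haenszel risk difference, or a centre term). If not, report a centre-stratified result as a sensitivity analysis only.

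Cost: some wording and programming and a few model terms. Demographics and D-dimer are already scheduled in Table 2. Ward type has no row of its own there and is assumed to be known from the enrolling department.

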#### Interim analysis {21b}

A total of 14 medical institutions will participate in this study, and the progress of the study is expected to be relatively rapid; therefore, no interim analysis is planned.

#### Methods for additional analyses (e.g. subgroup analyses) {20b}

Subgroup analyses are not planned.

#### Methods in analysis to handle protocol non-adherence and any statistical methods to handle missing data {20c}

For possible missing data during the study, the analysis will be carried forward for missing primary outcomes, and the specific carryover method is described in “Statistical methods for primary and secondary outcomes {20a}” section. Catheter occlusion is defined as a partial or complete occlusion of an intravascular catheter, resulting in blocked or restricted infusion of fluid or medication. For subjects who failed to complete the primary outcome evaluation, the method of worst-case imputation will be used to handle missing values. That is, if subjects withdraw early or for any other reason and the primary outcome is missing, the decision of whether or not catheter occlusion occurred will be treated as occlusion.

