In the control group, prefilled saline syringes containing 10 ml of 0.9% sodium chloride injection will be used to flush and lock the catheter via pulsatile flushing and the positive pressure locking technique. Before each infusion, the study nurses will mechanically wipe and sterilize the infusion connector. Catheter function will be assessed by flushing the catheters and aspirating for blood return. After seeing the blood return, the catheter will be flushed using short-interval pulsatile flushing (1 ml each time), for a total of 10 ml [22]. At the end of the infusion, prefilled saline syringes will be used to flush each lumen (even if only one lumen is used) via pulsatile flushing and the positive pressure technique [24].

The study will continue for 7 days unless there is catheter occlusion or catheter removal. During the 7 days, the study nurses will identify catheter occlusion by scoping the CINAS, observing the infusion status, and identifying the occlusion alarm. Once catheter occlusion occurs, the patients reach the end of the study, and the management of the blocked catheter will be referred to the physician and nurse. The end of the trial also includes a 2-day observation period, which will monitor the occurrence of catheter-related bloodstream infection (CRBSI), primarily through temperature monitoring.

Throughout the trial, the study team will fully respect the patient’s wishes, and the patients will have the right to withdraw from the trial. In addition, if a patient has no observed occlusion during the trial period and removes the CVC for other reasons, then the patient will be considered to have dropped out.

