#### Criteria for discontinuing or modifying allocated interventions {11b}

The intervention will stop in the following circumstances:

Patients who developed planned or unplanned catheter removal;Discharge, death, deterioration of the condition;Patients withdraw proactively;Wrong intervention.

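### Scoring every missing 7-day outcome as an occlusion turns catheters last known to be patent into events, cuts planned power from 80% to about 52%, and is not conservative for superiority

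*Protocol article*

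**What the plan says.** Four sections of the Protocol article combine to produce the rule.

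- Intervention description {11a}: a patient with no observed occlusion who "removes the CVC for other reasons, then the patient will be considered to have dropped out".
- Criteria for discontinuing or modifying allocated interventions {11b}: the first reason for stopping is "Patients who developed planned or unplanned catheter removal". Discharge, death, deterioration, withdrawal and wrong intervention follow. Section {18b} adds that tracking ends at discharge or transfer to another hospital.
- Statistical methods for primary and secondary outcomes {20a}: for subjects without a full efficacy evaluation, "non-responder imputation (NRI) will be used to handle the missing data". Superiority is concluded if the upper 95% confidence limit for the rate difference, test minus control, lies below 0. The analysis is done on both the FAS and the per protocol set (PPS), and neither is named as primary.
- Section {20c}: imputation is called worst-case and applies to early withdrawal or any other reason that leaves the primary outcome missing. In that case "the decision of whether or not catheter occlusion occurred will be treated as occlusion".

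Sample size {14} states: "An occlusion rate of 10% was assumed in the test group, and an occlusion rate of 25% was assumed in the control group". It uses a "single-sided significance level (*α*) at 0.025" and sets power "at 0.8 while taking into consideration a dropout rate of 20" per cent.

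**The concern.** A catheter that works until it is taken out on day 5 because it is no longer needed has given information, and that information is that no occlusion was observed. The rule replaces it with the opposite value. The primary rate then mixes two things: how often catheters occlude, and how often they come out, or the patient leaves, before day 7.

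Two consequences follow. First, adding the same share of events to both arms dilutes the difference, and the sample size does not allow for this. Second, an imputation that counts against both arms alike is not conservative for a superiority claim. Any excess of dropout in the control arm raises the control rate and helps the test arm; any excess in the test arm works against it. Participants and investigators are not blinded, and removal is a clinical decision, so the two arms need not have equal dropout.

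**Working it through.** **Inputs.** From Sample size {14}: control 25%, test 10%, one-sided alpha 0.025 (z = 1.96), power 0.80 (z = 0.8416), dropout 20%, 125 per arm. From {20a}: superiority if the upper 95% limit is below 0. Dropout by arm is not given, so every unequal split below is an assumption.

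**Step 1: reproduce the stated sample size.** Pooled formula, mean rate 0.175:

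n = [1.96·√(2·0.175·0.825) + 0.8416·√(0.25·0.75 + 0.10·0.90)]² / 0.15² = (1.053 + 0.443)² / 0.0225 ≈ 99.5, so 100 per arm.

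100 / (1 − 0.20) = 125, the stated figure. (The unpooled formula printed in {14} gives 97, then 97/0.8 = 122, which is close.) The 20% are thus treated as lost, leaving 100 evaluable patients per arm.

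**Step 2: apply the analysis rule.** With share d missing and occlusion rate p among the rest:

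analysed rate = d + (1 − d)·p

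- Control: 0.20 + 0.80·0.25 = 0.40
- Test: 0.20 + 0.80·0.10 = 0.28

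The difference shrinks from 15 to 12 points. Imputed events are 0.20/0.40 = 50% of control events and 0.20/0.28 = 71% of test events. Of the 25 imputed patients per arm, 25·0.75 ≈ 19 (control) and 25·0.90 = 22.5 (test) would not be expected to have occluded.

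**Step 3: power under the rule, 125 per arm, mean rate 0.34.**

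Power = Φ{[0.12·√125 − 1.96·√(2·0.34·0.66)] / √(0.40·0.60 + 0.28·0.72)} = Φ{(1.342 − 1.313)/0.665} = Φ(0.043) ≈ 0.52.

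Restoring 80% would take 244 per arm. At other equal dropout rates, power is 78% (5% dropout), 69% (10%) and 39% (30%).

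**Step 4: no true effect.** Chance of declaring superiority, by exact binomial enumeration with 125 per arm, using the confidence-limit rule:

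| Dropout control v test | True rate 25% in both | 15% in both | 10% in both |
|---|---|---|---|
| 20% v 20% | 2.6% | 2.6% | 2.6% |
| 22.5% v 17.5% | 8.9% | 11% | 12% |
| 25% v 15% | 23% | 31% | 36% |

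The pooled z test gives nearly the same values; for the last row they are 22%, 30% and 35%.

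**Step 5: true effect present, reverse imbalance.** With true rates of 25% v 10% and dropout of 15% control v 25% test:

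- Control: 0.15 + 0.85·0.25 = 0.3625
- Test: 0.25 + 0.75·0.10 = 0.325

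The chance of success is about 9%.

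**Step 6: the same patients, counting only observed occlusions.** With 20% leaving unoccluded in each arm, the rates are 0.80·0.25 = 0.20 and 0.80·0.10 = 0.08. Mean rate 0.14:

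Power = Φ{[0.12·√125 − 1.96·√(2·0.14·0.86)] / √(0.20·0.80 + 0.08·0.92)} = Φ{(1.342 − 0.962)/0.483} = Φ(0.786) ≈ 0.78.

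The difference is again 12 points, but the variance is much lower, so power stays close to plan.

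**The case against.** Several stronger readings are tempting, and the documents do not support them.

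- *Every stop listed in {11b} becomes an event.* Not so. That section says when the intervention stops; {20c} applies only when the primary outcome is missing. After a wrong intervention the catheter may stay in place, and nothing says patency checks end. Deterioration is similar. Removal after an observed occlusion is a real event.
- *Section {20c} contradicts itself.* It says "the analysis will be carried forward for missing primary outcomes", which could suggest last observation carried forward. But it refers to {20a} for the method, {20a} gives non-responder imputation, and {20c} then spells that rule out. This is loose wording, not a second rule.
- *The rule inflates type I error.* With equal dropout it does not, as step 4 shows. The documents give no dropout by arm and no stated reason to expect more control removals.

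Two further defences have some force. Section {18b} asks for patients expected to need the CVC for more than 8 days and keeps tracking in-hospital transfers, which should reduce missing outcomes. The protocol still plans for 20% dropout. The PPS may also exclude these patients, so disagreement between FAS and PPS could give a warning. But neither set is named as primary, and the PPS does not preserve the randomised comparison. A sensitivity analysis could be left to a SAP that is not shown; the rule itself is stated here and can be judged here.

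**Conclusion.** The point holds for patients whose 7-day outcome is missing, including those whose patent catheter is removed early, and for the FAS analysis.

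The firmest result needs only the protocol's own figures and dropout that is equal in both arms and unrelated to occlusion: power of about 52% against the stated 80%, with half or more of the events in each arm imputed. The cause is a mismatch: the sample size treats dropouts as lost, while the analysis counts them as events.

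False superiority is a conditional risk. At a 10-point excess of control dropout it would be about 22 to 30% if the common true rate is 25% or 15%, and about 36% if it is 10%. The opposite imbalance could leave a true effect with about a 9% chance of detection. These figures show how sensitive the rule is to unequal dropout; they do not predict what this trial will show. Because the rule decides the primary conclusion, it should be changed before the result is relied on.

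**What to change.** In the primary FAS analysis:

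- Count only observed occlusions as events.
- Treat removal of a catheter without observed occlusion, discharge and death as non-occlusion competing events. Use the removal record and the last available patency assessment. The participant timeline lists both kinds of data but does not promise a CINAS code at removal, so the analysis should not depend on one.
- Compare 7-day cumulative incidence between arms, for example with the Aalen-Johansen estimator, and decide on the 95% confidence interval of the difference. Without censoring this is simply observed occlusions divided by all FAS patients.
- Censor only true loss to follow-up with the catheter in place.
- Keep outcome data after a wrong intervention wherever patency is still assessed.

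Retain missing-as-occlusion as a sensitivity analysis. Add the real worst case for a superiority claim: missing counted as occluded in the test arm and as not occluded in the control arm. Replace the carried-forward wording in {20c} with the actual rule.

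The cost is modest extra analysis; no new data are needed. Trial status dates the end of data collection to July 31, 2023, so the change must be dated, with a statement of whether results by arm were known, and disclosed in the report.
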